## **2.2 Problem Statement**

Given high efficacy and effectiveness in other populations [16], demonstration projects of open-label PrEP in key populations – the highest risk groups – in Africa are needed to determine feasibility and acceptability of PrEP uptake and adherence. Key questions include: (i) whether those at substantial risk are motivated and able to initiate and sufficiently adhere to oral PrEP to achieve HIV prevention benefits; (ii) which delivery models are most effective; and (iii) how best to generate demand for PrEP in key populations without further stigmatizing them or PrEP use itself. The availability of information about PrEP across Africa has not been formally mapped but is likely suboptimal, both among general and key populations and among healthcare providers; ; and (iv) what their preferences are with regard to long-acting PrEP; if they are willing to use should it be made available and factors that may contribute to their uptake of long-acting injectable PrEP.

## **2.3 Rationale**

In a recent pilot study we conducted interviews and provided HIV testing and counselling (HTC) to 66 barmaids at 7 active bars in Kinondoni district, Dar es Salaam municipality (DSM). Only 4 of the 56 barmaids who completed HTC tested HIV positive (7.1%). Thirty-five percent of interviewed barmaids reported that they engage in sex for money with bar clients – although 80% reported that at least some barmaids in their bar engage in such behavior. In addition, 58% of respondents reported having had multiple sexual partners in the past year, over and above any relations with bar patrons. When asked, 54% of these barmaids stated they were either “very interested” or “somewhat interested” in taking a daily pill to protect against HIV; 61% of those who reported having sex with a bar client for money expressed this interest.

Based on these findings, we believe there is an urgent need to assess the feasibility of PrEP delivery for this population who have low HIV prevalence but are at high risk of HIV infection. In deciding who should be offered PrEP, needs and benefits (HIV prevention) should be balanced with harm (possible adverse events), costs, and feasibility. People who are at

substantial risk of acquiring HIV would achieve the greatest benefit from being able to access PrEP as an additional prevention choice. This study will also provide information on female barmaids' preferences long-acting injectable PrEP, if they are willing to use and factors both need and predisposing factors that need to be considered by stakeholders in implementation of long-acting injectable PrEP which is already in use in other countries.

## **2.4 Potential Risks and Benefits**

### **2.4.1 KNOWN POTENTIAL RISKS**

One risk for emtricitabine/tenofovir disoproxil taken as PrEP is that if someone is HIV-positive they may be at increased risk of developing resistance to the two active drugs. To avoid this we will test individuals for HIV at baseline, month 2 and month 4 during the trial. We will also conduct a detailed assessment of possible acute viral infection based on clinical symptoms; where such symptoms are present initiation will be delayed by one month and a second HIV test performed. Possible adverse reactions to emtricitabine/tenofovir disoproxil noted in its package insert include lactic acidosis/severe hepatomegaly with steatosis, exacerbation of Hepatitis B infection, onset or worsening of renal impairment and loss of bone mineral density. Following the WHO PrEP guidelines [17] Hepatitis B surface antigens will be clinically tested at baseline, with only individuals testing negative considered eligible for the trial. Individuals testing positive will be linked to specialized clinics for further testing and assessed for treatment. Serum creatinine levels will also be assessed at baseline to identify pre-existing renal disease, and at endline (6months). Only individuals with serum creatinine levels less than 60ml/min will be considered eligible to enroll in the trial. A range of other adverse reactions have been seen in clinical trials of emtricitabine/tenofovir disoproxil, including most commonly diarrhea, nausea, fatigue, headache, dizziness, depression, insomnia, abnormal dreams, and rash.

All of these risks are offset by the potential protection emtricitabine/tenofovir disoproxil provides against HIV acquisition in this very high-risk population of young women, who self-report very high levels of sexual activity with multiple partners, including a substantial minority reporting sex in exchange for money or goods. In Tanzania some health care providers from some health facilities have been trained on how to offer PrEP to customers.

Therefore, in this study some selected facilities with trained health care providers on how to offer PrEP in Tanzania will be selected to participate in this study.. Therefore, we will identify four facilities which provide PrEP and select some trained health care providers on PrEP to participate in this study.

---

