| Title:        | Demonstrating service delivery models for effective initiation and retention on PrEP among Barmaids in Dar es Salaam                                                                                                                                                                                                                                                                                                                                                                                                                                                                                                                                                                                                                                                                                                                                                                                                                                                                                                                                                           |
| Introduction: | 
In this double-randomized intervention study, participants will be provided with emtricitabine/tenofovir disoproxil as PrEP. Eligible participants will be randomized first to receive PrEP at their bar workplace or at a government clinic, and second to receive or not receive PrEP Champions intervention (physical and virtual support from an experienced PrEP user) to improve PrEP adherence.. We expect to screen 1204 barmaids in order to have at least 160 who are HIV negative and who agree to enroll in the study. After initial enrollment, follow-up visits will be scheduled every months. HIV testing will be performed at baseline, month 1, 4 and 6; TDF testing at months 2 and 6.
                                                                                                                                                                                                                                                                                                                                                               |

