## **5.2 Participant Exclusion Criteria**

- Report past diagnosis of renal disease
- Report past diagnosis of diabetes
- Report past diagnosis of hypertension
- Report current use of nephrotoxic medication
- Report flu-like symptoms that may represent acute HIV infection
- Report currently taking any of the following medications:
  - Any medicine containing emtricitabine or tenofovir disoproxil fumarate
  - Any medicine containing tenofovir alafenamide
  - Any medicine containing lamivudine
  - Adefovir
  - Didanosine
  - Atazanavir
  - Ledipasvir with sofosbuvir
  - Darunavir
  - Lopinavir with ritonavir
- Report bone pain or other bone problems
- Test positive for HIV or be unwilling to complete HIV counselling and testing.
- Test abnormally low for renal function using a serum creatinine test (<60ml/min).

- Test positive for Hepatitis B based on a hepatitis B surface antigen (HBsAg) test.

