### **5.4 Participant Withdrawal or termination**

#### **5.4.1 Reasons for Withdrawal or Termination**

Participants are free to withdraw from participation in the study at any time upon their requests and on their will without being forced or intimidated. The participants will be given clear explanation on the study, process and all procedures that will be done. The issue of withdrawal will be explained clearly that they can stop to participate in the study at any time and that their

withdrawal from the study will have no influence on how they will be treated or handled afterwards.

An investigator may terminate participation in the study (i.e. stop provision of PrEP) if:

- A participant tests positive for HIV
- A participants' renal function drops abnormally low
- Any clinical adverse event (AE), laboratory abnormality, or other medical condition or situation occurs such that continued participation in the study would not be in the best interest of a participant
- A participant ceases to work as a barmaid in Dar es Salaam

Apart from the above reasons for withdrawal or termination of participation in the study, the informed consent has a component that explains about stopping participation and that it will not impose any penalty to the participant.

---

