## **7.2 Laboratory Procedures/Evaluations**

All individuals willing to participate in screening will receive rapid HIV testing and counselling according to national guidelines [24]. Blood for Hepatitis B and baseline creatinine testing will be collected and sent to a local accredited laboratory at MUHAS, which will adhere to Good Clinical Laboratory Practice (GCLP) standards. Follow-up testing will occur as shown below.

| Visit                           | Onsite workplace test                  | Local laboratory test                                                |
|---------------------------------|----------------------------------------|----------------------------------------------------------------------|
| Recruitment and screening visit | HIV rapid test                         | Hepatitis B surface antigen test
Creatinine test
Syphilis test |
| Month 1                         | HIV rapid test                         |                                                                      |
| Month 2                         | TDF urine assay test                   |                                                                      |
| Month 4                         | HIV rapid test                         |                                                                      |
| Month 6                         | HIV rapid test
TDF urine assay test | Hepatitis B surface antigen test
Creatinine test
Syphilis test |

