#### **Follow-up Visit 1 (Visit 2, Day 60 +/- 7; Month 2)**

- Record adverse events as reported by participant or observed by investigator.
- Record vital signs, results of screening for Syphilis or other health conditions.
- Conduct urine tests TDF testing for adherence.
- Provide additional 28-days (1 month) supply of medication to the participant
- Record participant's adherence to treatment program.

- Re-counsel the participant on adherence to emtricitabine/tenofovir disoproxil and need to contact the study if any changes in health arise.
- Visit 2 will require between 1.5 and 2 hours to complete

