#### **Follow-up Visit 2 (Visit 4, Day 120 +/- 7; Month 4)**

- Record adverse events as reported by participant or observed by investigator.
- Record vital signs, or other health conditions.
- Conduct HTC including a rapid HIV test.
- Provide additional 28-day (1-month) supply of medication to the participant
- Record participant's adherence to treatment program.
- Re-counsel the participant on adherence to emtricitabine/tenofovir disoproxil and need to contact the study if any changes in health arise.
- Visit 4 will require between 1.5 and 2 hours to complete

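### Section 2.4.1 reverses the renal eligibility threshold of section 5.2 and gives HIV test months that disagree with the abstract and the schedules in sections 7.2 and 7.3

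*Protocol*

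**What the plan says.** **Renal rule.** Protocol section 2.4.1 (Known Potential Risks) says that serum creatinine is measured at baseline to find existing renal disease, and then: "Only individuals with serum creatinine levels less than 60ml/min will be considered eligible to enroll in the trial". Section 5.2 lists as an exclusion: "Test abnormally low for renal function using a serum creatinine test (<60ml/min" (the bracket closes there). Section 5.4.1 lets an investigator stop PrEP if a participant's "renal function drops abnormally low".

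**HIV tests.** To limit the risk of drug resistance in a woman who is HIV-positive, section 2.4.1 says "we will test individuals for HIV at baseline, month 2 and month 4 during the trial". The abstract (section 1) says "HIV testing will be performed at baseline, month 1, 4 and 6". Section 7.2 introduces its table with "Follow-up testing will occur as shown below"; the table has an HIV rapid test at screening and at months 1, 4 and 6. The visit lists in sections 7.3.1, 7.3.3 and 7.3.4 and the HIV row of the section 7.3.6 schedule agree with that table. At month 4 the visit list says "Conduct HTC including a rapid HIV test". At month 2 it says "Conduct urine tests TDF testing for adherence" and names no HIV test.

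**The concern.** Section 2.4.1 is where the protocol tells an ethics committee or a clinician how two named drug risks are kept in check: onset or worsening of renal impairment, and resistance when the drug is taken by someone with HIV. On the first, it states an eligibility threshold that points the wrong way. Anyone who followed that sentence would admit the women the safeguard is meant to keep out and turn away the rest. On the second, it describes a testing plan that omits the first and the last of the scheduled follow-up HIV tests.

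The renal sentence is more than loose background. It is worded as a rule on who may enroll. The direction of the cut also has a practical use after the first dose: creatinine is a laboratory test, and section 4.1 (Group 1b) offers immediate initiation at the bar, with later discontinuation if results show that an exclusion criterion is met.

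**Working it through.** The plan gives no figure to reproduce, so the check sets the texts side by side.

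**Renal rule**

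| Source | Below 60 ml/min | 60 ml/min or above |
|---|---|---|
| Section 2.4.1 | eligible | not eligible |
| Section 5.2 | excluded | not excluded on this ground |

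The set admitted by 2.4.1 is exactly the set excluded by 5.2. A woman below 60 fails 5.2, and a woman at 60 or above fails 2.4.1, so nobody passes both.

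Which text is wrong? Three things point to 2.4.1:

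1. Its own preceding sentence gives the purpose of the test as finding existing renal disease, which calls for excluding low function.
2. Section 5.2 attaches the value to abnormally low function, and section 5.4.1 treats low function as a reason to stop the drug.
3. One might try to rescue 2.4.1 by arguing that a low serum creatinine is a good sign. But ml/min is the unit of a clearance or filtration rate, not of a serum concentration, and for a clearance a low value is the bad one. Section 5.2 uses the same unit and cut with that meaning.

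**HIV tests, in months after baseline**

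| Source | Months |
|---|---|
| Section 2.4.1 | 2, 4 |
| Abstract | 1, 4, 6 |
| Section 7.2 table | 1, 4, 6 |
| Visit lists, sections 7.3.3 and 7.3.4 | 1, 4, 6 |
| Section 7.3.6 schedule | 1, 4, 6 (Visits 1, 4 and 6; Visit 2 blank) |

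All of them also have a test at screening or baseline. Comparing {2, 4} with {1, 4, 6}:

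- in both: {4}, 1 test;
- scheduled but missing from 2.4.1: {1, 6}, 2 of 3 tests;
- in 2.4.1 but not in sections 7.2 or 7.3: {2}, 1 test.

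The disagreement does not extend to creatinine timing. Section 2.4.1 gives baseline and 6 months, as do sections 7.2, 7.3 and 7.3.6.

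**The case against.** The best reply is that 2.4.1 is introductory and the operative sections are consistent. Sections 7.3.1 and 7.3.2 tell staff to check eligibility against the inclusion and exclusion criteria, so section 5.2 would probably govern. Section 5.2 also excludes women reporting past renal disease, diabetes, hypertension or current nephrotoxic medication, so renal protection does not rest on one sentence. Every detailed schedule gives the same HIV months. This stands as a limit on the likely harm. It does not make the renal sentence right: a protocol should not state an enrollment threshold in two opposite directions.

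A reader might infer more than the protocol supports:

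- **That women with impaired renal function will be enrolled.** The instruction to use the eligibility criteria makes this unlikely.
- **That a month-2 HIV test appears nowhere else in the protocol.** Section 4.1 (Group 1a) describes monitoring visits every two months that include HIV testing, and Group 1b follows the same visits. That could cover month 2. The text does not say at which visits the test is done, and it can be read as a summary of the whole visit series. The supportable statement is that sections 7.2 and 7.3 contain no month-2 HIV test.
- **That consent is affected.** Section 11.4.2 refers to 2.4.1 only for adverse effects of the pill, not for the renal cut or the test months, and the consent forms are not available here.
- **That the mismatch can be stated in days.** Section 2.4.1 gives months without visit windows, so the sets of months carry the whole point.

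**Conclusion.** Both contradictions hold. Section 2.4.1 reverses the renal threshold of section 5.2 and gives HIV test months that match only one of the three scheduled follow-up tests. The renal reversal matters more, because it is a wrong decision rule for a safety criterion; alone, the HIV mismatch would be close to editorial.

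No primary or secondary endpoint, sample size or power figure depends on either sentence. The exploratory count of HIV seroconversions at each visit (section 4.3.3) does depend on when tests are done, which is a further reason to have one stated schedule.

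The conclusion assumes that sections 5.2, 7.2 and 7.3 express the sponsor's intention. For the renal rule, the stated purpose of the test and section 5.4.1 make that close to certain. For the HIV months, it rests on the agreement of the abstract, the table, the visit lists and the schedule.

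**What to change.** In section 2.4.1:

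1. State that only women with creatinine clearance (or eGFR, whichever the sponsor intends) of at least 60 ml/min are eligible.
2. Change the HIV tests to baseline and months 1, 4 and 6.

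Two optional clarifications fit in the same edit: name the same ml/min quantity in section 5.2, and have section 4.1 refer to the section 7.2 table for the timing of HIV and creatinine tests.

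This changes wording only. It adds no test, visit or participant; the cost is the ethics review that section 11.3 requires for any amendment. If the sponsor does want an HIV test at month 2, the abstract and sections 7.2 and 7.3 would have to change as well. With the month-1 test kept, that adds one rapid test per participant, at most 160 × 1 = 160 tests at the planned enrollment.

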## 2.4.2 KNOWN POTENTIAL BENEFITS

PrEP has been shown to be effective for both men and women. There are studies which involved more than 17 000 people and have demonstrated an overall reduction in HIV acquisition risk of 51% (women relative risk (RR) 0.57; 95% confidence interval (CI) 0.34 - 0.94, and men RR 0.38; 95% CI 0.2 - 0.6). Three studies in which there was high adherence to the study product (>70% of drug detection) showed that PrEP was most efficacious and also that HIV infection was significantly reduced in those studies in which drug detection levels were moderate (41 - 70% detection) [18–20]. In the iPrEx study, a multinational study of HIV-seronegative men or transgender women who have sex with men and with evidence of high risk behavior for HIV-1 infection, Truvada was associated with a 42% reduction in HIV incidence [4,5]. In a trial of serodiscordant heterosexual couples in Kenya and Uganda (Partners PrEP) Truvada was associated with a 75% reduction in incidence of HIV in the seronegative partner [5].

## 3. STUDY OBJECTIVES

**Primary objective 1:** To assess whether workplace-based PrEP initiation for DSM barmaids at their bar of work increases the rate of PrEP initiation relative to initiation at healthcare facilities with the assistance of a peer navigator. This will be a person who is trained on social work and counseling (standard of care). Under existing Tanzanian national guidelines, workplace-based HIV testing is standard practice for those in high-risk populations, such as barmaids who often act as informal sex workers. Whether testing positive or negative for HIV, linkage to healthcare is also standard of care. However, self-linkage to HIV care after HIV diagnosis through community testing can be difficult, leading to loss to follow up. Previously, without support from a peer navigator, ART linkage rates in Dar es Salaam public-sector implementation projects have been as low as 30%. Standard of care in this trial will involve active linkage using peer navigators, however we propose to test whether immediate, on-site PrEP initiation leads to

higher rates of initiation compared to facility-based initiation following peer navigator-led active linkage.

**Primary objective 2:** To determine whether workplace-based initiation and provision of PrEP refills to barmaids in DSM at their bar of work increases PrEP retention and adherence relative to routine facility-based PrEP initiation and refilling at healthcare facilities. Under existing Tanzanian national guidelines, individuals must attend healthcare facilities to obtain refills of ART for treatment. This involves travel cost and waiting time at the clinic, and the potential for stigmatization by attending an HIV CTC. We therefore propose to determine whether having PrEP follow-ups conducted at barmaids' workplace (removing both travel and waiting) will lead to increased retention rates and improved adherence. To avoid possible social desirability bias, we will use urine samples for TDF testing as our primary retention and adherence outcome, since asking women to report their non-use of study HIV drugs has proven problematic in the past [21].

**Primary objective 3:** To assess barmaids' preferences, willingness to use, feasibility and factors for uptake of long-acting injectable HIV PrEP in Ubungu municipality, in-depth interviews will be conducted with barmaids who have used PrEP for about six months and those who have not been involved with PrEP intervention to learn about their preferences for delivery of and willingness to use long-acting injectable PrEP and factors that contribute to uptake of long-acting injectable PrEP. Also, Key informant interviews will be conducted with different stakeholders working in HIV interventions to understand their views on the feasibility of implementing long-acting injectable PrEP among barmaids, challenges in the implementation of PrEP pills programs and their preferences for service provision and factors that contribute to uptake of long-acting injectable PrEP.

**Secondary objective 1:** To determine whether being supported by an omni-channel (physical and virtual) PrEP Champion, who provide support and information to clients, improves adherence and retention. Depending on feasibility (owning a smartphone) and preferences of the participants, they will receive physical and/or virtual support from the responsible PrEP Champion who will regularly share standardized informative media with the participants to improve their PrEP knowledge and provide adherence support. We propose to evaluate whether the program omni-channel PrEP Champions is an effective and feasible method to improve

adherence in a high-risk population. We will use self-reported adherence as our effectiveness outcome for this objective, to capture drug use across the whole study period, rather than the shorter window captured by urine-based testing. We will use in-depth interviews with respondents, and key informant interviews with the PrEP Champions, to evaluate the feasibility of omni-channel PrEP Champions, including with respect to rolling it out more widely.

**Secondary objective 2:** To document the performance of a novel point of care urine assay as a measure of adherence to PrEP. Current tests for adherence to tenofovir – an active agent in PrEP- are predominantly blood (plasma/antibodies) or hair based [22,23]. These traditional methods are invasive and require specialized personnel, equipment and laboratory facilities [22,23]. The University of California San Francisco (UCSF), in collaboration with Alere Rapid Diagnostics have developed a low-cost rapid urine assay that does not require specialized equipment or training. This urine-based assay has been shown to be sensitive (96%), specific (100%) and precise (<15% coefficient of variation) in previous studies [22,23]. The present trial will utilize this point-of-care urine assay and document its performance in a real-world setting.

